#### Aim 1b

2.6.2

The primary analysis will employ a linear mixed model with surgery versus medication as the independent variable to compare the effect of treatment on communication, behavior, and quality of life. A similar analytic approach will be used for secondary analyses comparing early versus later use of treatment. We will select nonsurgical comparison patients to be matched to surgical patients on a variety of factors that are associated with the choice of therapy. Should we be unable to match certain factors, we will consider separate multivariable adjustments. We will use generalized linear mixed models, with appropriate link and distributional assumptions, and will allow for the separation of within-site and between-site variance components. Results will be reported with and without adjustment for potential confounders. If our final sample size is not adequate for such statistics, we at minimum will provide a baseline descriptive analysis of the results.

#### Aim 2

2.6.3

We will describe patterns of use and will conduct comparative effectiveness analyses of epilepsy surgery and LGS-approved medications across the multiple sites. In parallel with analyses in Aim 1a, we will consider surgical versus medication pathways as well as CC and VNS separately. We will also explore all epilepsy surgery including cranial epilepsy surgery, CC, VNS, DBS, and RNS to understand the spectrum of real-world care. Results will be summarized overall and by factors of interest (e.g., center, age, race, ethnicity, health insurance, medical complexity). Health insurance will be categorized as public, private, or self-pay. Exploratory analyses will be conducted for comparisons. For categorical variables, proportions will be reported, and Chi-square tests or Fisher’s exact tests will be used to assess independence. For continuous variables, means and standard deviations will be reported, and t-tests will be performed to evaluate independence. These data will provide context for interpreting the generalizability of the analyses performed for Aims 1a and 1b.

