### Study aims

2.1

Aim 1: Determine the effect of epilepsy surgery and LGS-approved anti-seizure medications on two key clinical outcomes in children with LGS.

a. Compare the effectiveness of the addition of surgeries versus the addition of another medication for reducing seizure-related emergency healthcare utilization.

b. Compare the effectiveness of these two pathways and of early versus later use of surgery versus medications on measures of children’s expressive communication, behavior, and quality of life.

Aim 2: For individuals with LGS, describe real-world utilization of these treatments across multiple centers in the US, and identify variability including disparities that may currently pose challenges and barriers to ensuring optimum access to and use of appropriate therapies.

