#### Aim 1b

2.2.2

In a cross-sectional study across the 7 high-intensity sites, we will evaluate the two treatment pathways regarding expressive communication, behavior, and parent-reported quality of life of patients with validated diagnoses of LGS, and the impact of earlier (younger age) versus later (older age) utilization of the therapy. Caregivers will complete a series of surveys to assess their child’s communication, behavior, and quality of life.

#### Aim 2

2.2.3

In a retrospective cohort study across all 18 sites, we will analyze patterns of utilization of surgeries versus additional medication. We will also assess variation in their use across sites by age, race, ethnicity, health insurance, and overall medical complexity. Aim 2 will use the computable phenotypes for LGS that are developed from the intensive coding validation with EHR review and clinical diagnosis adjudication in the retrospective study cohort in Aim 1a.

Institutional Review Board (IRB) review for this protocol will be conducted at each study site, or in some cases via reliance upon a PEDSnet IRB protocol. All aspects of the study (Aims 1a, 1b, and 2) have received approval from the IRB of Ann & Robert H. Lurie Children’s Hospital. This study is registered at www.ClinicalTrials.gov (NCT05374824).

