### Sample size estimates

2.5

Preliminary data exploration across the 7 high-intensity sites identified an average of over 200 pediatric patients with LGS per site. Based on this, we anticipate a total sample size of more than 3,600 with ICD-10 diagnosis code G40.81x and, after sampling, chart review, and recruitment, approximately 464 participants for Aim 1b. We expect that approximately one-third will be in the surgery arm.

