The primary analyses will compare epilepsy surgery (CC or VNS, CC alone, VNS alone) to the addition of another LGS-approved medication. We also will compare CC to VNS. While CC and VNS are the most common surgeries, we will also explore all epilepsy surgeries including cranial epilepsy surgery, CC, VNS, DBS, and RNS to addition of another LGS-approved medication, to understand VNS and CC in the spectrum of care. We will use a generalized linear mixed model with Poisson distribution and log link to compare the frequency of ED visits and inpatient admissions in the 6 months post-intervention. To guard against any potential biases in the selection of the type of surgical therapy or of surgery versus medication that might arise due to medical complexity, we will employ inverse probability of treatment weighting (IPTW), which uses the propensity score/conditional probability to balance baseline patient characteristics across different treatment groups. Treatment selection will be modeled with a logistic regression using information available at the time the decision is made like age, sex, pediatric complex chronic conditions (PCCC) (39), and anti-seizure medication use. The inverse of the resulting probability will be used to weight each individual in regression models for the outcomes. PCCC scores, reflecting medical complexity, will be calculated from existing data provided by each site. Based on our knowledge of and experience with LGS and its treatment, we do not expect large differences between the patients receiving the different types of therapies. We will describe what the differences are that appear to influence the selective use of these different therapies.

A random site effect will account for clustering within sites. Robust standard errors will be used to control for mild violation of distributional assumptions. In the case of severe violations, a Negative Binomial or zero-inflated Poisson model may also be considered. We will report the conditional rate ratios that estimate the expected rates of ED visits and separate hospitalizations in the surgery arm compared to the medication arm for the 1-year and 2-year periods following intervention. Additionally, a combined variable representing overall emergency healthcare utilization, including both ED visits and inpatient admissions, will be considered.

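### Aim 2 looks for disparities across 18 sites with tests that carry no site or covariate term, so between-site differences cannot be told apart from within-site race or insurance differences

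*Protocol article*

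**What the plan says.** Section 2.1 gives Aim 2 the task to "identify variability including disparities that may currently pose challenges and barriers to ensuring optimum access to and use of appropriate therapies". Section 2.2.3 sets the scale: "In a retrospective cohort study across all 18 sites, we will analyze patterns of utilization of surgeries versus additional medication". It continues: "We will also assess variation in their use across sites by age, race, ethnicity, health insurance, and overall medical complexity".

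Section 2.6.3 (Data analysis, Aim 2) labels the comparisons exploratory and names the tests. Categorical factors get chi-square or Fisher's exact tests; this is the operative rule for race, ethnicity and insurance. Continuous factors get this: "For continuous variables, means and standard deviations will be reported, and t-tests will be performed to evaluate independence". Center appears once, in a list of factors by which results will be summarized. It is neither a stratum nor a model term. No adjustment for other patient factors is mentioned for these comparisons.

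The other two aims treat site differently. Section 2.6.1 (Aim 1a) has inverse probability weighting and says "A random site effect will account for clustering within sites". Section 2.6.2 (Aim 1b) uses mixed models that split variance into within-site and between-site parts, and reports results with and without confounder adjustment.

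**The concern.** Aims 1a and 1b draw on 7 sites and model site. Aim 2 draws on 18 and is the aim concerned with variation across them, yet its named tests contain no site term. This is a stated method, not a detail that a condensed article has left out.

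Two things can go wrong if centers differ both in how often they operate and in whom they serve. First, patients within a center resemble one another on both variables, so the independence assumption fails and p-values are too small. Second, a crude association by race or insurance mixes two different situations: patients of one group attend centers that operate less, or they are offered surgery less often than others at the same center. The first points to referral and access between centers, the second to decisions inside a center. A two-way test cannot say which is present. Nor can it say whether an insurance difference remains once age and medical complexity are taken into account.

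**Working it through.** **Inputs from the article.** 18 sites (2.2.3). About 200 patients per site: section 2.5 says that exploration of the 7 high-intensity sites "identified an average of over 200 pediatric patients with LGS per site". The anticipated total is more than 3,600, which reproduces as 18 x 200 = 3,600 (7 x 200 = 1,400 does not). The surgery share is one-third (2.5); it is stated directly after the Aim 1b figure, so its use for Aim 2 is an assumption.

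**Inputs assumed.** The article gives no between-site variation and no alpha for Aim 2. Assumed: public insurance share 50%, two-sided 5% level, and normal site effects on the logit scale, drawn independently for surgery and for payer mix.

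**Model.** For site k, logit P(surgery) = logit(1/3) + a_k and logit P(public) = logit(1/2) + b_k. Within a site, surgery and payer are independent, so the true within-site odds ratio is 1.

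What the SDs mean: logit(1/3) = -0.693. With SD 0.25, sites one SD either side of the average have surgery shares of 1/(1+e^0.943) = 28% and 1/(1+e^0.443) = 39%. With SD 0.5 they have 1/(1+e^1.193) = 23% and 1/(1+e^0.193) = 45%. For payer, SD 0.8 gives 1/(1+e^0.8) = 31% to 69% public.

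**Tests.** Pooled chi-square on the 2x2 table: N(AD - BC)^2 / [(A+B)(C+D)(A+C)(B+D)], compared with 3.841. Site-stratified Cochran-Mantel-Haenszel (CMH): [sum(y1k - Ek)]^2 / sum(Vk), with Ek = n1k tk/m and Vk = n1k n0k tk(m - tk)/[m^2(m - 1)]. Here m = 200, n1k and n0k are the public and other patients at site k, tk is its surgeries, and y1k is its surgeries among public patients.

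**Rejection rates at nominal 5%.**

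| Site SD, surgery / payer | Pooled chi-square |
|---|---|
| either SD 0 | about 5% |
| 0.25 / 0.25 | 5.3% to 5.5% |
| 0.25 / 0.5 | 7.0% |
| 0.5 / 0.5 | 10.7% to 11.4% |
| 0.5 / 0.8 | 18.3% to 18.5% |
| 0.75 / 1.0 | 36.2% |

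Ranges are separate simulation runs. The site-stratified test stayed at about 4% to 6% throughout. The last row is a wide assumption, shown only as an outer bound.

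For a continuous factor compared between surgery and medication, with surgery SD 0.5, the t-test rejects 5.5%, 6.9% and 10.7% at site intraclass correlations of 0.01, 0.02 and 0.05. A within-site test stayed at 4.4% to 5.7% over all settings.

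**Worked example.** Nine sites (1,800 patients) have 40% surgery and 35% public insurance. Nine sites (1,800) have 26.7% surgery and 65% public.
- Public: 630 x 0.40 + 1,170 x 0.267 = 252 + 312 = 564 of 1,800 (31.3%).
- Other: 1,170 x 0.40 + 630 x 0.267 = 468 + 168 = 636 of 1,800 (35.3%).
- Pooled odds ratio: (564 x 1,164)/(1,236 x 636) = 0.84.
- Chi-square: 3,600 x (656,496 - 786,096)^2 / (1,800 x 1,800 x 1,200 x 2,400) = 6.48, p = 0.011.

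Within every site the odds ratio is exactly 1. The whole difference lies between sites, and the named test does not reveal that.

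**The case against.** The strongest reply is that Aim 2 is largely descriptive. Section 2.6.3 calls the comparisons exploratory and says that they give context for the generalizability of Aims 1a and 1b. A crude difference is then a proper quantity to report. If publicly insured children attend centers that operate less, that is itself an access disparity, and a model that only adjusts for site would hide it. This stands. The crude proportions should stay, and site adjustment alone is not the remedy. It does not rescue the p-value, or a reading of it as a patient-level effect, and disparities are a stated aim rather than a by-product.

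The simulation does not simply count real between-site disparities as errors. Site effects for surgery and payer were drawn independently, so any alignment across the 18 sites is chance. For those 18 sites alone the alignment is a fact; as evidence about care more widely, it is not.

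It is also fair that the SDs are assumptions, that 200 per site comes from the 7 high-intensity sites, and that the absence of a site term is read from what the section names.

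Two stronger readings are tempting and lack support:
- A reader might infer that a two-sample t-test would be applied across 18 centers or three insurance classes. The section never says so. Its contrasts are two-group ones (surgery versus medication, CC and VNS), for which a t-test on age is ordinary.
- A reader might infer that the unadjusted tests will also serve the effectiveness comparisons, because the section "will conduct comparative effectiveness analyses of epilepsy surgery and LGS-approved medications across the multiple sites". The tests are not assigned to those outcomes, and the text places Aim 2 in parallel with Aim 1a, so the Aim 1a weighted model may well carry over.

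**Conclusion.** The point holds for the utilization and disparity comparisons of Aim 2. The named tests assume independent patients, adjust for nothing, and cannot separate within-site from between-site differences, although the aim concerns disparities across 18 sites.

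The size is conditional. The distortion needs both surgery use and patient mix to vary between sites. Over the assumed SDs from 0.25/0.25 to 0.5/0.8, a nominal 5% chi-square test rejects about 5% to 18% of the time with no within-site association. It is negligible at the low end and absent if either quantity is constant across sites. The document does not show where the real data fall, so it does not support saying that the Aim 2 results will be wrong. The primary comparisons in Aims 1a and 1b are unaffected. The change is worth making because it is cheap and bears directly on what Aim 2 is meant to show.

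**What to change.** 1. Keep the crude proportions, means and simple tests, by factor and by center, and label them as descriptive.
2. Add a mixed-effects logistic model of surgery versus medication with a random site intercept and age, race, ethnicity, insurance and medical complexity.
3. For each factor of interest, add its site mean (for example, the share of publicly insured patients at the site). The patient-level coefficient then gives the within-site difference and the site-mean term carries the between-site one. Report both, so that access disparities between centers are not adjusted away.
4. State in section 2.6.3 that the Aim 2 comparative effectiveness analyses use the Aim 1a weighted mixed model, if that is the intention.

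The cost is a few sentences of wording and a modest amount of extra analysis in standard software. Section 2.4.3 already extracts center and all the covariates. One limit should be stated when reporting: the between-site terms rest on 18 sites and will be imprecise.

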## Discussion

3

While various treatment options exist for LGS, there have not been comparative effectiveness studies regarding epilepsy surgery versus additional medications for LGS patients who do not respond to initial treatments. Clinical guidelines for LGS focus on medications (14, 40–42). Treatment decisions are often guided by judgment based on a clinician’s own experience (6, 43). Decisions are also made by comparing the results of drug trials conducted in different eras, in different settings, using different selection criteria, and sometimes with different definitions of LGS (17, 18). For epilepsy surgery, the level of evidence is weak, including uncontrolled retrospective and prospective studies showing before-and-after comparisons (15, 20–24). Our study will fill this gap by providing head-to-head comparisons among the potential therapies used for LGS (44, 45).

### Computable phenotype

3.1

Validation of ICD-10 coding for LGS based on review of the EHR and clinician adjudication has not been previously published. It can be challenging to accurately diagnose LGS. The clinical presentation of the syndrome evolves, and the definition of LGS has changed over time (6, 44–47). There is a wide range of presentations, and the time period before the characteristic features of LGS manifest varies between individuals (6, 8, 44–46, 48). Many of the features of LGS overlap with those of other severe epilepsies, which can lead to misdiagnosis or delayed diagnosis (46), and can affect treatment decisions and outcomes. The definition of LGS in trials has also varied, which makes it difficult to fully interpret the effectiveness of treatments (17, 18, 43). We aim to develop methods to classify patients consistently and accurately within large datasets. Such phenotypes would facilitate future large-scale LGS studies that may lead to new insights into the treatment of LGS. They may also enable more accurate diagnosis of LGS in the clinical setting.

### Community-engaged research

3.2

Engaging patients and their families in research is an important component of our study. The patient and family journey is a critical motivating factor and is indeed the basis of this project. Engagement enhances the overall quality of research by improving the relevance and applicability of study outcomes (49). A Stakeholder Advisory Board (SAB) consisting of clinicians, caregivers, patients, and patient advocates is working together with the investigator team to help generate research questions, assist in the conduct of research, monitor progress, and help disseminate information. The primary purpose of the SAB is to ensure that the study design and research activities are patient-centered and informed by and relevant to patients and families with lived experience. As an example, a series of focus groups will be conducted together to select the survey instruments for outcome measurements to be used for Aim 1b.

### PCORnet® data

3.3

This study will also enhance PCORnet®‘s infrastructure and capability to conduct research on LGS and other rare pediatric epilepsies by developing a robust platform and network for future research. We will establish a multi-site pediatric epilepsy research group that will engage with patients, parents, and community stakeholders. Creating a comprehensive database and collaboration among 18 sites will facilitate large-scale studies that were previously unattainable for these rare conditions. This network will support collection and analysis of high-quality data, promote sharing of resources among researchers, and improve understanding of data provenance and data quality for pediatric epilepsy research in PCORnet®. Through intensive reviews of medical records, we will improve techniques for computable phenotyping of LGS. We seek to harmonize such phenotyping across the leading US centers for pediatric epilepsy.

### Limitations

3.4

There are limitations. Retrospective studies can have bias due to incomplete or inaccurate historical data. The reliance on self-reported survey data in Aim 1b can lead to response and recall biases. The open cohort design can introduce selection bias due to participants entering at different times. These factors may limit the ability to draw definitive conclusions and may affect the generalizability of our findings. Future research should aim to address these limitations by incorporating prospective data collection. Nevertheless, this is the first national scale comparative effectiveness study addressing the choice of epilepsy surgery or additional anti-seizure medications: the study is designed to address outcomes that matter to patients and families and will inform future patient-centered LGS research including prospective studies.

Previously, this study proposal approved for PCORI sponsorship was entitled, “Comparative effectiveness of palliative surgery versus additional anti-seizure medications for Lennox–Gastaut Syndrome.” There is growing recognition in the field that the terminology of palliative epilepsy surgery needs to be updated: while treatment is not expected to be curative, outcomes of reduced seizure burden and improved quality of life can be worthwhile and life-changing. The historical and common use of the term palliative epilepsy surgery may be misleading for epilepsy care, and we shall be mindful to rectify the terminology in ongoing and future dissemination efforts. To this end, we have submitted a request to revise the study title to “Comparative effectiveness of epilepsy surgery versus additional anti-seizure medications for Lennox–Gastaut Syndrome,” and we have removed the use of the term “palliative” in this manuscript.

The study design is strengthened by validation and adjudication of the diagnosis of LGS. Since our cohort will be representative of a broader community of LGS patients who receive care at sites across the US, our results will be more robust and more generalizable than those in the existing literature. We also will provide the broad community of stakeholders with evidence describing current LGS treatment patterns across 18 centers. This study will strengthen patient/family engagement and epilepsy research collaboration across the US and will help describe variability, disparities, and opportunities to improve care and care coordination.

### Ethics and dissemination

3.5

The study will be reviewed and approved by the IRB initially at Ann & Robert H. Lurie Children’s Hospital and subsequently at each of the study sites, in some cases via reliance upon a PEDSnet IRB protocol. Participants will provide informed consent to participate in Aim 1b.

Algorithms or methods developed to assist the creation of computable phenotypes for LGS will be transmitted to the Phenotype Knowledgebase website (PheKB, www.phekb.org). All materials developed for activities involving our leadership, patients, and stakeholders will be shared and archived in the Patient-Centered Outcomes Research Institute Engagement Tool and Resources Repository. Copies of programming codes used to derive the data sets and to perform the analyses will also be made available. The data dictionary containing variable names and labels, codes and their meanings, and branching logic will be made available as well. Study resources will also be made available through PCORI-recommended mechanisms. Dissemination of study design, review of interim results, calls for ongoing input, and reports of findings will be done in collaboration with the LGS Foundation and the broader communities.

The PEDSnet data used for this study was provided by PEDSnet and can be shared only with approval from the PEDSnet consortium and an appropriate Data Use Agreement.
